## Abstract

**Background:**

In The Netherlands, helmet therapy is a commonly used treatment in infants with skull deformation (deformational plagiocephaly or deformational brachycephaly). However, evidence of the effectiveness of this treatment remains lacking. The HEADS study (HElmet therapy Assessment in Deformed Skulls) aims to determine the effects and costs of helmet therapy compared to no helmet therapy in infants with moderate to severe skull deformation.

**Methods/design:**

Pragmatic randomised controlled trial (RCT) nested in a cohort study. The cohort study included infants with a positional preference and/or skull deformation at two to four months (first assessment). At 5 months of age, all children were assessed again and infants meeting the criteria for helmet therapy were asked to participate in the RCT. Participants were randomly allocated to either helmet therapy or no helmet therapy. Parents of eligible infants that do not agree with enrolment in the RCT were invited to stay enrolled for follow up in a non-randomisedrandomised controlled trial (nRCT); they were then free to make the decision to start helmet therapy or not. Follow-up assessments took place at 8, 12 and 24 months of age. The main outcome will be head shape at 24 months that is measured using plagiocephalometry. Secondary outcomes will be satisfaction of parents and professionals with the appearance of the child, parental concerns about the future, anxiety level and satisfaction with the treatment, motor development and quality of life of the infant. Finally, compliance and costs will also be determined.

**Discussion:**

HEADS will be the first study presenting data from an RCT on the effectiveness of helmet therapy. Outcomes will be important for affected children and their parents, health care professionals and future treatment policies. Our findings are likely to influence the reimbursement policies of health insurance companies.

Besides these health outcomes, we will be able to address several methodological questions, *e.g.* do participants in an RCT represent the eligible target population and do outcomes of the RCT differ from outcomes found in the nRCT?

**Trial registration:**

ISRCTN18473161.

## Background

Infants have malleable and fast-growing cranial bones, and are therefore at risk of developing skull deformation if their head often remains in the same position. When a child turns its head toward one side most of the time, this is defined as positional preference [1]. Skull deformation due to such prolonged external forces (non-synostotic) must be distinguished from skull malformation due to premature fusion of the cranial sutures (synostotic) [2]. Deformational brachycephaly refers to a symmetric occipital flattening of the skull that is sometimes accompanied by temporal bossing or an occipital lift [3]. The term deformational plagiocephaly is used to describe a unilateral occipital flattening of the skull. More severe cases often present with ear misalignment and facial asymmetry [2,4].

Skull deformation is generally considered a purely cosmetic disorder. Yet parents worry that the deformation might be permanent and might influence the child’s attractiveness with the risk of, for example, being teased [5]. Some studies suggest long-term developmental delays due to skull deformity, but no causal relationships have been found [5-7].

The prevalence of skull deformation can be up to 21.5% in infants younger than 6 months, but decreases within the first years of life [8-10]. A low parental level of education, ethnicity, male gender, primiparity, prematurity, birth factors, delayed (motor) development, low activity level and several positioning and dietary factors have been reported as risk factors, while placing a child in the prone position when awake appears to be a protective factor [1,11-17].

Prevention or treatment of positional preference and skull deformation include parental counselling, counter-positioning and physical therapy [10,18]. Children with persisting severe skull deformation at the age of 5 to 6 months are commonly treated using orthotic devices (redression helmets or headbands) [4,19]. In The Netherlands, a redression helmet costs about €1,200 and is reimbursed by health insurance companies as well as the accompanying visits to the (paediatric) physician. However, until now, no randomised controlled trials (RCTs) have been performed to study the effectiveness of this therapy [20,21]. The few non-randomised studies tend to show positive results, but have several limitations. To start with it is unknown whether the reported differences in effectiveness are clinically relevant. Furthermore, follow-up in these studies was short-term (either directly after treatment or just a few months afterwards), there was a lack of blinding or information about blinding and often no validated outcome measures were used. Finally, data about complications were not collected in a structural way in these studies [2,4,20,22,23]. Although the known complications of helmet therapy are mild and do not seem to occur often, the treatment burdens both parents and their young children [22]. Next to the lack of scientific evidence, experience shows differences in beliefs and referral policies of health care professionals regarding helmet therapy. Some advocate the use of helmets to treat skull deformation, while others are reluctant to prescribe this intensive treatment for a cosmetic condition without knowing its effectiveness [21,24]. This makes parents very uncertain when they have to decide whether to start helmet therapy or not.

Both helmet therapy and no helmet therapy (allowing natural recovery) are standard approaches in The Netherlands. To compare the effectiveness of these two approaches a pragmatic RCT study design is required [25]. Pragmatic trials are designed to find out the effectiveness of a treatment in routine, everyday practice and thereby have a high external validity [26,27]. A high external validity can be achieved by recruiting a broad study population that is representative of the target population, studying interventions that approach a real world delivery of care, applying blinding to neither participants nor specialists and selecting a wide range of outcome measures [28,29].

Since the condition of interest changes over time and the decision-making is time-dependent, the RCT needs to be nested in a cohort study [30-32]. The decision to start helmet therapy is usually taken at 5 to 6 months of age. Recruitment at that stage is complicated as the children tend to be scattered among various institutes if their parents prefer helmet therapy or are outside the health care system if their parents choose not to start helmet therapy. As the cohort study recruits children at risk of disease progression before helmet therapy can be prescribed, we tackle this problem and we are also able to predict the number of children that ultimately will be eligible for helmet therapy and identify prognostic factors.

Additionally, nesting the RCT in a prospective cohort study makes it possible to present information on the representativeness of the RCT population, by comparing this population with non-participants [33,34]. Furthermore, outcomes of the randomised trial can be compared with the parallel non-randomised trial that employs the same types of intervention.

The main goal of the Helmet Therapy Assessment in Deformed Skulls (HEADS) study is to investigate the effects and costs of six months of helmet therapy compared to no helmet therapy in children with moderate to severe skull deformation. This article describes how this study is designed and reports the recruitment scheme so far. We provide a description of the statistical analysis plan to be used after data collection is completed and conclude with general recommendations on study design.

## Methods/design

### Study design

The HEADS study is a two-armed pragmatic RCT nested in a cohort study (Figure 1). The intervention is redression helmet therapy; the control condition is no helmet therapy (allowing natural recovery). The study starts as a cohort study for children aged two to four months with a positional preference and/or skull deformation (T0). At five months of age (T5), follow-up assessments are performed and parents of children with a moderate to severe skull deformation are invited to participate in the RCT. Eligible children whose parents do not wish to enrol in the RCT are invited to join the non-randomised controlled trial (nRCT) that runs parallel to the RCT. In both studies, follow-up assessments are performed at eight (T8), twelve (T12) and twenty-four months (T24) of age.

**Figure 1 F1:**
[figure not shown]
**Flow chart of participants in HEADS.** Provisional data.

Ethics approval for the study was given on the 8th January 2009 (ref: NL24352.044.08) by the Medical Ethics Committee of the Medisch Spectrum Twente hospital in Enschede, The Netherlands.

### Recruitment & setting

Participants were recruited (April 2009 to present) and measured by specially trained paediatric physical therapists (HEADS PPTs) in the Eastern part of the Netherlands (in the provinces of Drenthe, Overijssel and parts of Gelderland).

In The Netherlands, all infants are screened in the first months of life for positional preference and skull deformation at well-baby clinics. Youth Health Care professionals working at well-baby clinics in the region where the study is carried out have been informed about this study, reminded to look for this condition and asked to refer cases to HEADS PPTs.

There are 96 HEADS PPTs involved in the study, working in 73 physical therapist practices. They all received three instruction sessions from the researchers of the HEADS study, including theory lessons on positional preference and skull deformation, a refresher course about plagiocephalometry (PCM) assessment and training in recruiting patients for RCTs.

Based on their experience and performance in the HEADS study, six HEADS PPTs were selected to perform the assessments at T24 (T24-HEADS PPTs) and received an extra instruction session.

Children could be treated with helmet therapy at ProReva (Zwolle), Deventer Hospital/LIVIT (Deventer) and Slingeland Hospital/Roessingh Rehabilitation Technique (Doetinchem). At the start of the HEADS study, these were the only institutions providing helmet therapy within the region in which the project is carried out, and therefore they were asked to collaborate in the RCT. Parents of children in the nRCT could also choose institutions outside of this region or newer institutes that provide helmet therapy within the region.

### Eligibility criteria

#### *Cohort study*

Children aged two to four months with a positional preference and/or skull deformation are eligible for the cohort study. Premature children (gestational age below 36 weeks), children with congenital muscular torticollis, craniosynostosis and/or dysmorphic features are all excluded.

#### *Randomised controlled trial*

Children aged 5 months with a moderate to severe skull deformation, measured by PCM are eligible for the RCT. PCM is a reliable, valid, non-invasive and easy-to-use method for measuring the shape of the skull [35,36]. To determine the severity of deformational plagiocephaly, the oblique diameter difference index (ODDI) is used. This is the ratio between the longest and the shortest oblique diameter, multiplied by 100%. Both diameters are located at 40° from the anterior-posterior line. A moderate to severe plagiocephaly is defined as 108% ≤ ODDI ≤ 113%. The severity of deformational brachycephaly is established with the cranio proportional index (CPI). This is the ratio between the width and the length of the skull and is considered to be moderate to severe when 95% ≤ CPI ≤ 104%. Mixed forms with ODDI > 106% and CPI > 92% are also included. Exclusion criteria are similar to those at T0.

At T5, children meeting RCT eligibility criteria can still enrol in the study (late-enrolment).

#### *Non-randomised controlled trial*

Children eligible for the RCT, but whose parents declined participation, are invited to participate in the nRCT for follow-up. Children with PCM outcomes above the upper thresholds of the inclusion criteria for the RCT are also asked to participate in the nRCT.

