### Population

Figure 1 shows that 883 infants enrolled at T0 for baseline measurement. At T5, 808 infants had a follow-up assessment; 477 did not meet the inclusion criteria for the RCT. Of these 477 infants, 26 infants had PCM outcomes above the upper thresholds of the inclusion criteria for the RCT and were eligible to participate in the nRCT. Seventy-five infants enrolled at T5 via late-enrolment, of whom 5 infants had PCM outcomes above the upper thresholds of the inclusion criteria for the RCT and were eligible to participate in the nRCT. Of the eligible 401 infants, 84 (21%) were recruited for the RCT, 296 did not participate in the RCT because their parents declined to enrol them, but were recruited for the nRCT (74%) and 21 (5%) were not recruited to either of the studies. Parents signed an informed consent form before participation in the cohort study, as well as before participation in the RCT.

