#### *Comparison between the randomized and the non-randomised controlled trials*

Baseline characteristics will be compared between the RCT and the nRCT. To study differences in the continuous as well as the dichotomous variable between the RCT and the nRCT, both a multiple linear regression analysis and a logistic regression analysis will be carried out, with the interaction factor of study (RCT or nRCT) × group (helmet or no helmet).

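### The RCT-versus-nRCT comparison is not limited to RCT-eligible infants, so it can mix a severity difference with the effect of study design

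*Protocol article*

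**What the plan says.** All references are to the protocol article.

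- **Eligibility criteria, Randomised controlled trial.** Each index has an upper bound (figures in per cent). For plagiocephaly: "A moderate to severe plagiocephaly is defined as 108% ≤ ODDI ≤ 113". For brachycephaly, the CPI "is considered to be moderate to severe when 95% ≤ CPI ≤ 104". A third route has no stated upper bound: "Mixed forms with ODDI > 106% and CPI > 92% are also included".
- **Eligibility criteria, Non-randomised controlled trial.** Besides infants whose parents declined the RCT: "Children with PCM outcomes above the upper thresholds of the inclusion criteria for the RCT are also asked to participate in the nRCT".
- **Population.** Of the 808 cohort infants seen again at T5, 477 fell outside the RCT criteria, and the article separates out the most severe among them: "Of these 477 infants, 26 infants had PCM outcomes above the upper thresholds of the inclusion criteria for the RCT". Five of the 75 late enrolments were also above the limits.
- **Comparison between the randomized and the non-randomised controlled trials.** Linear and logistic regression are planned "with the interaction factor of study (RCT or nRCT) × group (helmet or no helmet"). The section restricts neither population and names no severity covariate. It does plan a comparison of baseline characteristics.
- **Abstract and Study design.** Both describe the nRCT only as eligible infants whose parents did not want randomisation, which is narrower than the eligibility section.

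**The concern.** The Discussion part of the Abstract asks whether RCT and nRCT outcomes differ, and the main Discussion wants to learn from this how useful non-randomised data are. That question needs the same kind of infant in both studies, so that the way treatment was assigned is what differs. Here the eligibility rules build in a second difference, because the nRCT may contain infants whom the RCT turned away as too severely affected.

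Both forms of the primary outcome depend on the starting value. An infant further from normal has more room for absolute change and further to go to reach the full-recovery cut-offs. Treatment in the nRCT is chosen by parents, so helmet uptake may also rise with severity. An interaction could then be read as a consequence of not randomising when part of it is case mix. The two outcomes could even be pulled in opposite directions: towards the helmet on the change score and away from it on full recovery.

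**Working it through.** **1. Reproduce the plan's own count.** RCT-eligible infants at T5: (808 − 477) + (75 − 5) = 331 + 70 = 401, as stated. Their destinations: 84 RCT + 296 nRCT + 21 neither = 401. Both sums are exact, so the above-limit infants are not among the 296.

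**2. Share of the nRCT.** Above-limit infants: 26 + 5 = 31. If all enrolled, 31/(296 + 31) = 31/327 = 9.5%. If they enrolled at the rate of the eligible infants, (84 + 296)/401 = 380/401, then 31 × 380/401 = 29.4 and 29.4/325.4 = 9.0%. The article gives their eligibility, not their enrolment, so 9.5% is a ceiling.

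**3. Why severity matters for the outcomes.** Full recovery requires ODDI < 104% and CPI < 90% (Primary outcome).

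| Starting value | Fall needed |
|---|---|
| ODDI 108% | more than 4 points |
| ODDI above 113% | more than 9 points |
| CPI 95% | more than 5 points |
| CPI above 104% | more than 14 points |

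**4. Shift in the nRCT change-score contrast from unequal uptake.** The article gives no inputs for this, so they are assumptions. Let h be helmet uptake in the 296 in-range infants, k uptake in the 31 above-limit infants, and D the extra ODDI change of above-limit infants in either arm. The above-limit share is

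- helmet group: s1 = 31k / (296h + 31k)
- no-helmet group: s0 = 31(1 − k) / (296(1 − h) + 31(1 − k))

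and the unadjusted helmet-minus-none contrast shifts by D × (s1 − s0).

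| h | k | s1 − s0 | D = 2 | D = 4 | D = 6 |
|---|---|---|---|---|---|
| 30% | 80% | 0.189 | 0.38 | 0.76 | 1.14 |
| 30% | 100% | 0.259 | 0.52 | 1.04 | 1.55 |
| 50% | 80% | 0.103 | 0.21 | 0.41 | 0.62 |
| 50% | 100% | 0.173 | 0.35 | 0.69 | 1.04 |
| 70% | 80% | 0.042 | 0.08 | 0.17 | 0.25 |
| 70% | 100% | 0.130 | 0.26 | 0.52 | 0.78 |
| any | equal to h | 0 | 0 | 0 | 0 |

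**5. Shift if the helmet effect itself differs.** With equal uptake and a helmet effect E points larger above the limits, the nRCT effect shifts by E × 31/327: 0.19, 0.38 and 0.57 for E = 2, 4 and 6.

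**6. Scale.** The Sample size section plans for a difference of 4 ODDI points with SD 6. With that SD, equal RCT arms, 63 to 72 RCT infants, 222 to 296 nRCT infants and a helmeted fraction f of 30% to 50% (assumed), the interaction has SE = 6 × √(4/n_RCT + 1/(f·n_nRCT) + 1/((1 − f)·n_nRCT)) = 1.58 to 1.75 points. The 95% CI is then about ±3.1 to ±3.4 points (1.96 × SE).

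**The case against.** The strongest reply is that the point rests on silence. The comparison section names a model, not an analysis set, and a condensed article may leave such detail to the full protocol. The regressions may also adjust for severity. This stands only in part. The article states both the wider nRCT eligibility and the model, and following them as written puts the above-limit infants into the comparison. Adjustment would help, but for infants above the limits it leans largely on extrapolation from the RCT range.

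Other objections stand and limit the claim:

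- A reader might infer that all 31 are more deformed than any RCT infant. The text does not support this, because the mixed-form route has no upper bound. An infant with ODDI 115% and CPI 93%, for example, meets it as written.
- The limits are on two indices and the split of the 31 is not given. An infant over only the CPI limit may have no extra ODDI change, so giving all 31 an extra change is an upper-end assumption.
- Even the largest shift in the table (1.55) is below one standard error of the interaction (1.58 to 1.75).
- A reader might infer that the nRCT's own analysis must also be restricted. That would be a preference. Parental choice exposes the 296 in-range infants to confounding by indication as well, and a broad real-world group is a stated aim.
- A reader might suppose that the plan treats a non-significant interaction as proof of agreement. It nowhere says so.

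**Conclusion.** The point holds for the RCT-versus-nRCT comparison only. As written, that comparison can include up to 31 infants (at most 9.5% of the nRCT) who were excluded from the RCT for exceeding its upper limits, so study design and severity are partly mixed. The likely distortion of the change-score contrast is modest: roughly 0 to 1.6 ODDI points against a planned difference of 4. It is zero if neither helmet uptake nor helmet effect varies with severity.

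That range rests on assumed uptake (30% to 70% in range, 80% to 100% above the limits, or equal uptake), an assumed 2 to 6 points of extra change or extra effect, enrolment of all 31, no covariate adjustment, and each mechanism taken alone. The size for full recovery was not calculated. The randomised primary analysis does not use these infants and is not in question.

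**What to change.** In the section comparing the two studies:

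1. Make the main analysis one of infants meeting the RCT eligibility criteria in both parts (84 RCT, 296 nRCT).
2. Repeat it with the full nRCT as a sensitivity analysis, and describe the above-limit infants separately, including how many enrolled.
3. State how being above the upper limits is decided for mixed forms, for which the RCT criteria give none, and bring the descriptions of the nRCT in the Abstract and Study design into line with the eligibility section.
4. Report the interaction estimate with its 95% CI.

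The nRCT's own analysis may keep all participants. The cost is a few sentences of analysis wording and up to 31 fewer infants in the main comparison. No new data are needed.

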### Population

Figure 1 shows that 883 infants enrolled at T0 for baseline measurement. At T5, 808 infants had a follow-up assessment; 477 did not meet the inclusion criteria for the RCT. Of these 477 infants, 26 infants had PCM outcomes above the upper thresholds of the inclusion criteria for the RCT and were eligible to participate in the nRCT. Seventy-five infants enrolled at T5 via late-enrolment, of whom 5 infants had PCM outcomes above the upper thresholds of the inclusion criteria for the RCT and were eligible to participate in the nRCT. Of the eligible 401 infants, 84 (21%) were recruited for the RCT, 296 did not participate in the RCT because their parents declined to enrol them, but were recruited for the nRCT (74%) and 21 (5%) were not recruited to either of the studies. Parents signed an informed consent form before participation in the cohort study, as well as before participation in the RCT.

### Randomisation

A computer-generated blocked randomisation plan with blocks of eight participants is used to allocate treatment in the RCT. After a HEADS PPT enrols a child for the RCT, he or she informs the researcher ([name]) who contacts the parents. Both parents and researcher are unaware of allocation until the parents have signed the informed consent form and confirmed participation. The researcher performs the allocation and informs the parents about group allocation. The child’s HEADS PPT, general practitioner and Youth Health Care professional are also informed about the allocation afterwards.

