### Blinding

Blinding of parents and professionals to allocation is not possible during the intervention period, including the T8 and T12 assessment. To ensure unbiased long-term outcomes, the T24 assessments are blinded. These assessments are carried out by T24-HEADS PPTs, who are unfamiliar with the history of the infants they are measuring. Furthermore, we instruct parents in the invitation letter and a poster at the assessment location, not to mention group allocation to the assessor.

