### Sample size

The required sample size for the HEADS RCT, based on a significance level of 5%, power of 90% and a difference in mean improvement of at least 4 ODDI-points (SD 6 ODDI-points) was calculated as 72 infants (36 in each arm). Assuming a maximum estimated loss-to-follow up of 25%, we needed to include 96 children in the RCT.

In 2008, a preliminary study was performed into the feasibility of an RCT on helmet therapy for skull deformation. Of the parents of 61 children with a skull deformation, 39% agreed to participate in a study as described in the patient information and verbally clarified. In the light of this information, the size of the current study region was chosen and the inclusion period was estimated.

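### With a fixed block of eight, a recruiting researcher who knows the block size could deduce about one allocation in five before consent, so the researcher's stated unawareness is not secured

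*Protocol article*

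**What the plan says.** The Randomisation section fixes the scheme: "A computer-generated blocked randomisation plan with blocks of eight participants is used to allocate treatment in the RCT". It mentions one plan, no stratification and a single block size.

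The same section sets out the order of events. "After a HEADS PPT enrols a child for the RCT, he or she informs the researcher", and the researcher then contacts the parents. After consent, "The researcher performs the allocation and informs the parents about group allocation". On concealment it states: "Both parents and researcher are unaware of allocation until the parents have signed the informed consent form and confirmed participation".

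The Blinding section adds: "Blinding of parents and professionals to allocation is not possible during the intervention period, including the T8 and T12 assessment". The Population section reports: "Of the eligible 401 infants, 84 (21%) were recruited for the RCT". A further 296 infants, whose parents declined the RCT, joined the non-randomised study. The Sample size section plans 96 randomised infants, from 72 evaluable with 36 per arm. The Recruitment & setting and Trial status sections show that enrolment was still open when the article appeared.

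**The concern.** The person who speaks to parents before they commit is also the person who has made and announced every earlier allocation. In a block of known, constant size, the earlier allocations determine the later ones as soon as one arm is full. The last place in a block is always determined, and sometimes the places just before it are too. Someone who knows the block size and keeps the tally can therefore know certain allocations before consent is signed, which is what the quoted statement says does not happen.

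Concealment of the next allocation is what makes the randomised arms comparable. If encouragement to sign differed, even unintentionally, with the expected arm and the infant's severity, the arms could differ in prognosis from the start. The blinded assessment at 24 months protects the measurement of head shape. It does not protect the choice of who was enrolled.

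**Working it through.** The article gives no predictability figure, so there is none to reproduce.

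**Inputs**
- Block size 8, constant (Randomisation).
- 4:4 within each block. This is an inference from the equal arms of 36 in the Sample size section; the Randomisation section gives no ratio.
- One list. This is an inference from the singular wording and the absence of strata.
- 84 recruited (Population); 96 planned (Sample size).
- The researcher knows all earlier allocations. This follows from performing and announcing each one.
- The researcher knows the block size and keeps the tally. This is an assumption; the article does not say so.

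**Allocations that are certain in advance**

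There are C(8,4) = 70 equally likely blocks. Position k is determined if one arm already has its four infants among the first k − 1 places. The number of such blocks is 2 × C(k − 1, 4):

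| Position | Blocks in which it is determined | Probability |
|---|---|---|
| 1 to 4 | 0 | 0% |
| 5 | 2 × 1 = 2 | 2.9% |
| 6 | 2 × 5 = 10 | 14.3% |
| 7 | 2 × 15 = 30 | 42.9% |
| 8 | 2 × 35 = 70 | 100% |

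Expected number per block = (2 + 10 + 30 + 70)/70 = 112/70 = 1.6, and 1.6/8 = 20%. The closed form 2m/(m + 1) with m = 4 gives the same: 8/5 = 1.6.

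**Applied to this trial**
- 84 infants = 10 full blocks + 4. The first four places of a block are never determined, so the expected number is 10 × 1.6 = 16.0 (19.0%).
- 96 infants = 12 full blocks: 12 × 1.6 = 19.2 (20.0%).
- Still to come on the current scheme: 96 − 84 = 12 places, with 19.2 − 16.0 = 3.2 determined.

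**Guessing when the allocation is not certain**

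Guessing the arm that is behind in the block, and tossing a coin when the arms are level, gives 4 + (2^8/70 − 1)/2 = 4 + (3.657 − 1)/2 = 5.33 correct of 8, or 66.6%. Without block knowledge the figure is 50%.

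**Sensitivity to the one-list reading**

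With three separate lists, 84 infants are 28 per list (3 blocks + 4): 3 × 3 × 1.6 = 14.4, or 17.1%. For 96 (32 per list) the result is again 19.2, or 20%. The conclusion barely depends on this reading.

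**The case against.** The strongest reply is that the article asserts unawareness and nothing in it says otherwise. Deduction requires a researcher who knew the block size and tracked position and arm totals, and the article states neither. It also does not say who generated or held the list, and a condensed article may leave that to the full protocol. This stands in part: nobody can conclude from the text that concealment failed. It does not remove the weakness. Sealed envelopes or a list held elsewhere would not prevent end-of-block deduction by someone who knows the block size and the earlier allocations, and the block size is in print while recruitment continues.

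A reader might also infer that the researcher's conversation explains the split of 296 infants in the non-randomised study against 84 in the RCT, so that the scope for steering is wide. The documents do not support this. A HEADS PPT first enrols the child, and there are 96 of them in 73 practices. They are told of their own child's allocation only afterwards. How many families dropped out between the researcher's contact and signed consent is not reported, and many refusals may have come before it. The exposed step is of unknown size.

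Finally, the Statistical analyses section compares the arms on prognostic factors and plans ANCOVA and regression with predictor variables. That helps with measured factors, including severity at five months. It does not reach unmeasured ones.

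**Conclusion.** The point holds as a conditional design weakness. With 4:4 blocks and a researcher who knows the block size and follows the count, an expected 20% of allocations are deducible before consent: 16.0 of 84 so far and 19.2 of 96. The procedure described therefore does not secure the researcher's stated unawareness. The parents' unawareness is not in question, since they cannot see the sequence.

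A reader might go further and infer that concealment was broken or that the comparison is biased. The article shows neither: it does not report what the researcher knew, nor any selective enrolment. What can be said is that the scheme leaves an avoidable opening at the step between PPT enrolment and signed consent, in a trial small enough for a few selectively enrolled infants to matter.

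**What to change.** For the remaining allocations:

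1. Replace the constant block with randomly varying block sizes that the recruiting researcher does not know. A smaller fixed block would make things worse: the same calculation gives 25% determined for blocks of six and 33.3% for blocks of four.
2. Have an existing team member who does not speak to parents hold the list and release each allocation only after signed consent is registered.

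For the infants already randomised:

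3. Qualify the statement of unawareness. Say whether the researcher knew the block size and, if so, that about one allocation in five could have been deduced.
4. Optionally, describe baseline ODDI and CPI by arm for deducible and other allocations, noting that about 16 deducible infants are too few to exclude selection.

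The cost is a regenerated list, a change of who releases allocations, and a short descriptive table. The downside is a possible small imbalance in final arm sizes: leaving the open block after four of its eight places could by itself leave a difference of up to four infants. The gain is also limited, because only about 12 places, with about three expected determined allocations, remain on the article's provisional count.
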